### Data collection and management

Investigators will collect and manage data locally at each site; subsequently, all data will be securely transferred to Unit 1 for quality controls and analysis.

### Scientific output

The first scientific manuscript for the PEOPLHE project will describe the baseline round results, including the strategies used to prompt the enrollment of screenees. Subsequent papers will detail the impact of collateral and incidental findings, and how many diagnostic procedures were requested for findings other than lung cancer (Fig. 1).

**Fig. 1 Fig1:**
[figure not shown]
Template of the structured report used within the PEOPLHE project. The first section summarizes the findings: including this information as the first paragraph was intended to increase readability and comprehension for both GPs and screenees; contact details are reported to allow easy interaction with the researchers. Subsequently, we designed a second paragraph including detailed results of LDCT reading (focused on both pulmonary nodules and other findings). The last section of the structured report includes data on radiation exposure and the study protocol.

### Ethics

The Institutional Review Boards of each Unit approved the study protocol. Before each baseline LDCT, written information on benefits and harms of LCS will be provided and informed consent will be obtained from all screenees. The study was conducted carefully following the indication from Dlgs 101/20 on radiological screening. Participants will be informed about the goals of LCS, along with its potential positive and negative consequences and limitations.

## Discussion

The convincing evidence of LC mortality reduction in large randomized controlled trials ought to European endorsement of LCS implementation. Italy does not currently have a LCS program, but its implementation is being discussed and will be supported by analysis of other ongoing LCS programs [20]. PEOPLHE will address several important issues relevant to the implementation of LCS. It will aim at apportioning the workload and capacity needed for implementation of LCS, including lung cancer screening outcomes and the clinical management of incidental findings. PEOPLHE will also assess the effect, if any, of invitation to LCS has on smoking rates, which was heterogeneous in previous studies and it is known to be subject to bias related to selecting people willing to engage in a research study for health improvement [21–23]. The information from three tertiary Italian hospitals located in different geographical areas is expected to cover a range of geographical and organizational variables.

*Administrative and organizational needs.*

A major LCS challenge is represented by the lack of systematic and coordinated support, especially for a site first approaching LCS activities, which would be the potential situation of almost all Italian hospitals [24]. By reporting the experience of three academic hospitals, we aim to identify the needed up-front infrastructural and manpower investments.

*Enrollment and engagement strategies.*

Identified barriers hampering LCS participation include travel issues or psychological factors (anxiety and stigma), which negatively impact a person’s motivation to attend [25, 26]. Uptake and adherence disparities were potentially related to structural barriers preventing receipt of equitable care, lower socioeconomic status and difficulties in obtaining reimbursements [27–29].

Participation of high-risk populations can be enriched through tailored communication strategies with several invitation approaches, or by offering a mobile setting [30, 31]. The PEOPLHE trial will test the role of telephone triage to present the trial, foster participation of screenees, and organize LCS appointments. A similar approach was previously proposed by the Yorkshire Lung Screening Trial (YLST) in the United Kingdom [7]. Centralization of LDCT in a tertiary hospital is the way to specialized thoracic radiologists and state-of-the-art technology (high-performance scanner, CAD tools, and volumetric nodule measurement). Moreover, the use of mobile CT scanners is associated with higher costs and it seems that scanner location is not the main determinant of LCS uptake [32].

Notably, a minor trust in LCS has been recently reported to challenge LCS implementation in the US, while knowledge of LCS guidelines is a strong and independent predictor for a higher likelihood of suggesting LCS by several healthcare providers [29, 33]. To increase the awareness of the advantages related to LCS, the PEOPLHE staff organized several meetings, both online and in-person, with GPs and other healthcare providers, seeking support from local health associations for recruiting screenees, as well as social media campaigns [34]. A similar role for these health associations has been endorsed by Swiss experts [35].

Previous literature reported generally large rates of drop-out from LCS [36]. We will assess the need for human and financial resources to ensure screenees engagement. Focused analyses of drop-off from LCS based on LDCT outcome categories will be performed, as previous experiences reported higher rates of “no-shows” in subjects with baseline Lung-RADS 3 to 4 as compared with Lung-RADS 1 to 2 [37]. Although potentially affected by the relatively limited time-span of our study, we will explore whether the possibility of low adherence after the baseline round can be counteracted by an NSLT-like active approach, including the administration of annual questionnaires on smoking habit and periodic telephone calls and e-mails.

*Smoking cessation.*

Smoking cessation is the most effective strategy for reducing LC mortality and morbidity. A legitimate concern arose about the possibility that current smokers might consider LCS as a surrogate for an excuse to continue smoking, due to reassurance from a “negative” LDCT. On the other hand, LCS can positively affect smoking cessation among smokers who undergo screening and anti-tobacco counselling [38, 39].

Combined psychological and pharmacologic support have been reported to increase quit rates, with favorable cost-effectiveness ratio when antismoking therapy of natural origin is introduced or when smoking cessation services are proposed immediately after a Target Lung Health Check [14, 40]. However, rates of decline have slowed, and certain categories, namely “hardcore smokers” including smokers less willing to quit, heavy smokers, and who exhibit high-level nicotine dependence, show resistance to tobacco control measures [41–43].

PEOPLHE—by integrating a strict anti-tobacco activity—will record the number of subjects quitting smoking, and the characteristics of both quitters and “hardcore smokers”, expanding the available literature on the topic with potential perspectives on strategies to improve quitting.

*LDCT acquisition, reading and reporting.*

Current recommendations suggest annual LCS throughout a long-time span (up to 25 years) [3] LDCT-based LCS might be associated with the potential risk of radiation-induced LC [44]. Balancing the positive impact of LCS on LC mortality with the risks of radiation exposure is one major focus of LCS literature. Recent improvements in CT hardware and software fostered a great interest in reducing the radiation burden beyond the current state-of-the-art in thoracic imaging (LDCT) toward imaging at a calculated radiation dose of below 1 milliSievert, termed ultra-low-dose CT (ULDCT) [45, 46].

The cost-effectiveness of LCS might vary substantially as it is implemented in real-world settings depending on screenees’ selection, false-positive rate, and rates of invasive procedures. Two independent radiologists have usually performed LCS reading, causing an increased cost for LC [47]. Therefore, the implementation of CAD tools within the workflow can reduce costs and reduce variability in detection rates, with the advantage of reducing the risk of false-negative LDCTs, especially for small pulmonary nodules and nodules in peri-hilar regions [20, 48, 49].

LDCT reports produced in the PEOPLHE trial will be standardized, containing all information bolstered by the European Society of Thoracic Imaging (ESTI) [50]. The PEOPLHE LDCT report has been developed to minimize misunderstandings between screenees and healthcare providers. The outcome and suggested management are clearly stated in the first paragraph, followed by more detailed information; during dedicated phone calls from healthcare providers (trained radiology residents, data managers, experienced radiologists), indeterminate and positive findings and further actions (including the timing of follow-ups or additional investigations) will be discussed.

The PEOPLHE program will provide relevant information on administrative and organizational needs for implementation of lung cancer screening within national healthcare system.

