## Material and methods

### Study design

PEOPLHE is a three-year multicentric project supported by the Italian Ministry of Health (MOH) (RF-2019-12371462).

PEOPLHE aims at recruiting 1.500 high-risk individuals across 3 tertiary general hospitals (500 screenees for each center) that are community-based and provide comprehensive services to large populations of three Italian regions, including thoracic oncology multidisciplinary team. The multicentric design aims at exploring geographic, demographic, and socioeconomic diversities that might hamper the implementation of Italian LCS practice.

Selection criteria were derived from the NELSON trial [9], as follows: (i) 50–75 years of age; (ii) smoking habit of > 15 cigarettes/day for > 25 years or > 10 cigarettes/day for > 30 years; (iii) current or former smoker quitting < 10 years; (iiii) no history of cancer in the previous five years.

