### Screenees enrollment

PEOPLHE enrollment focuses on a) systematic recruitment of eligible subjects, b) involvement of general practitioners (GP), c) efficiency of referral to LCS hub, and d) capacity needs.

Noteworthy, PEOPLHE was designed before the pandemic of severe acute respiratory distress syndrome coronavirus 2 (SARS-CoV-2), when the peripheral network of GPs was hypothesized to leverage LCS toward the population. However, this structure needed to be converted to cope with the increased workload following the pandemic. Furthermore, tailored approaches are needed to guarantee safe management of patients, screenees and healthcare personnel [10].

The informative campaign rolled out at different levels:*Media* level: local and institutional newspapers, social media pages, local television networks on health-dedicated shows. Dedicated informative events were hosted during national anti-tobacco days.*Hospital* level: flyers and roll-ups of the PEOPLHE trial reporting study objectives, inclusion criteria, and contacts (email, phone, and QR code toward the subscription website) were placed in the radiology and pneumology departments of the three Units.*Healthcare providers* level: dedicated conferences involving local GPs, pulmonologists, and any healthcare provider.

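### The effect of screening invitation on smoking cannot be identified from a single enrolled cohort with no comparator

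*Protocol article*

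**What the plan says.** In the protocol article, the opening of the Discussion states that "PEOPLHE will also assess the effect, if any, of invitation to LCS has on smoking rates". The same sentence says of this effect that it was heterogeneous in previous studies and that "it is known to be subject to bias related to selecting people willing to engage in a research study for health improvement".

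The Discussion paragraphs on enrollment and engagement make two related statements. The first is that "The PEOPLHE trial will test the role of telephone triage to present the trial, foster participation of screenees, and organize LCS appointments". The second, on drop-off from screening, is that "we will explore whether the possibility of low adherence after the baseline round can be counteracted by an NSLT-like active approach", the approach being yearly smoking questionnaires with periodic calls and e-mails.

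The design behind these statements is set out elsewhere:

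- **Study design:** 1,500 screenees, 500 at each of three hospitals. No allocation or comparison group is described.
- **Screenees enrollment:** a campaign through media, hospital material (e-mail, phone and a "QR code toward the subscription website") and conferences for healthcare providers.
- **Smoking cessation (Methods):** questionnaires at baseline, 12 and 24 months; researchers also point participants to anti-smoking centres at baseline and recall rounds.
- **Abstract, Methods:** current smokers are offered cessation support.

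**The concern.** The effect of invitation on smoking is a contrast between smoking in people who were invited and smoking in comparable people who were not. The article describes only people who enrolled. What it can deliver is the proportion of enrolled smokers who have stopped by 12 and 24 months, which is a different quantity.

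The sentence that makes the claim also names the selection bias of earlier work, but no design feature in the article removes that bias here. Naming it does not make the effect estimable.

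The programme is meant to inform national implementation, including the need for smoking cessation facilities. If a fall in smoking is reported as an effect of invitation, planners may count on a benefit from inviting people that in fact reflects motivated volunteers, quitting that would have happened anyway, or the cessation support. In the same way, good attendance could be credited to calls and e-mails without a contrast to support it, in a programme that also sets out to assess the resources needed to keep screenees engaged.

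**Working it through.** **1. The stated size.** 3 centres × 500 screenees = 1,500, which agrees with the stated total. The article gives no power, significance level or effect size, so there is no sample-size figure to recompute. The question is identifiability, not power.

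**2. Search for a comparator.** For each statement, the comparison group it would need is set beside what the article describes.

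| Statement | Group needed | Described in the article |
|---|---|---|
| Invitation and smoking | People not invited, or an external or historical series | None; smoking is recorded in participants only |
| Telephone triage and participation | Eligible people approached without triage | None |
| Active contact and adherence after baseline | Participants without active contact | None; the only adherence comparison announced is by LDCT outcome category |

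No section mentions randomisation, a staggered start or an outside control series.

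**3. What the before-after change contains.** Write the observed quit proportion as

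observed = background quitting in these volunteers + cessation support + screening itself + invitation.

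The cohort supplies the left-hand side only. One equation cannot separate four terms. Self-selection acts through the first term: people who come forward for a health study may quit more often than other smokers.

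**4. Illustration of size (all inputs assumed).** Assume that 50% to 80% of the 1,500 are current smokers at baseline, which is 750 to 1,200 people, and that 5% to 20% quit. The 95% half-width is 1.96 × √[q(1 − q)/n].

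- Smallest: q = 0.05, n = 1,200: 1.96 × √(0.0475/1,200) = 1.23 points.
- Largest: q = 0.20, n = 750: 1.96 × √(0.16/750) = 2.86 points.
- At q = 0.10: 1.70 points (n = 1,200) to 2.15 points (n = 750).

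Now assume 10% observed quitting, with 0 to 10 points coming from the terms other than invitation. The part due to invitation is 10 − 0 = 10 points at one end and 10 − 10 = 0 points at the other. The quit proportion would be estimated fairly precisely, and that precision says nothing about its cause.

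**The case against.** The strongest reply is that this is a feasibility programme. The Introduction says that it is intended to describe. All three sentences stand in the Discussion and none is a listed objective. The Discussion paragraphs on smoking cessation already state the output descriptively, as a count of quitters and the characteristics of quitters and of resistant smokers. The triage and active-contact sentences are also milder: one speaks of testing a role, the other of exploring, with a caveat about the short time span. Both can be read as uptake among people telephoned and attendance under active contact.

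Most of this stands, and it limits the point to overstated inference rather than a failed primary objective. It does not rescue the smoking sentence, which names an effect of invitation that the design cannot give. An analysis plan could not supply an unexposed group within a single cohort. A full protocol might name an external comparator, but nothing in the article points to one.

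Three stronger readings should be resisted:

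- **That every participant receives triage, calls and e-mails.** The article does not say so. It lists e-mail, phone and a QR code as contact routes and does not state who gets periodic calls. Only the questionnaires are scheduled for the cohort.
- **That nobody is individually invited.** The enrollment section names systematic recruitment, general practitioners and referral to the hub. It says that the practitioner network had to be converted after the pandemic, and neither describes nor excludes individual referral.
- **That nothing can be estimated.** Quit proportions, uptake after calls, adherence by LDCT category and differences between units can all be described. What is missing is a causal contrast.

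**Conclusion.** The smoking sentence is wrong as written: a single cohort of enrolled volunteers, who are also offered cessation support if they smoke, cannot show the effect of invitation on smoking rates. The same limit applies, less sharply, to any conclusion that triage raised participation or that active contact offset low adherence.

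The size of the possible error cannot be derived from the article. Under the assumed figures above it could be the whole of an observed change. This conclusion rests on the article describing no comparator, and it would change if the full protocol defined one.

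A reader might infer that the programme needs a randomised comparison of contact methods. The documents do not support making that a requirement: the programme is descriptive and already under way, and accurate wording is enough to resolve the point.

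**What to change.** 1. **Discussion, opening:** replace the claim about invitation with *change in smoking status among enrolled participants from baseline to 12 and 24 months, not attributable to invitation*. This matches the descriptive aim already given in the Discussion under smoking cessation.
2. **Discussion, enrollment and engagement, triage:** present telephone triage as a described process, reporting calls made and uptake among the persons telephoned. The denominator is people contacted before enrolment, not people enrolled.
3. **Discussion, enrollment and engagement, adherence:** report adherence after baseline as a rate observed under active contact, overall and by LDCT category, and draw no conclusion that active contact counteracted low adherence.
4. If the full protocol does define an external comparator for smoking, name it here instead.

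The first three changes are wording only. They need no new participants or contacts, and the smoking questionnaires stay as planned. Item 2 assumes that calls and their outcomes are logged. The cost is that the programme gives up three causal conclusions that its design could not have supported.
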